### Randomization

Participants will be randomized after the baseline visit and before the planned first day of program use. All V0 and V1 data for each participant must be fully monitored, with all queries resolved, before randomization may take place. We will use a randomization server (sealedenvelope.com) that implements the random permuted blocks within strata procedure [49, 50] with strata as age (*Older Adults 65–74* or *Older Adults* ≥ 75 years of age), allocation ratio is 1:1. Participants who are randomized to the experimental treatment group will also be randomized to either receive version 1 (experimental treatment with performance feedback) or version 2 (experimental treatment without performance feedback); at the mid-training assessment, participants will undergo a reversal of the version type such that all participants completing the entirety of the training will have trained on both versions of the experimental training program. The Site Coordinating Center will issue a randomization assignment at the appropriate time. This approach represents a best practice approach to randomization, implementing an automated centralized group assignment procedure with allocation concealment, and effective separation of sequence generation and allocation concealment.

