## Methods

### Overall design and timeline

The current study will employ a multi-site, longitudinal, blinded randomized controlled trial (RCT) design with a target sample of 120 older adults without dementia or MCI (see inclusion criteria below). Sixty older adults completing TAPAT will be compared to sixty older adults completing the active control condition (computer-based games; see Fig. 1). Total participation time is approximately 6 months and includes 5 in-person assessment sessions. Assessments will be performed at University of Iowa (Iowa City, IA) and VA Boston Healthcare System (Boston, MA). The first assessment session (V0) involves screening for eligibility (see inclusion/exclusion below). If the participant is eligible, baseline assessments are administered in a second visit (V1) to characterize their cognitive and functional abilities before training. After the baseline assessment, older adults are randomized to either the TAPAT or control training program and complete approximately 12–16 weeks of in-home training, while monitored and coached by a research assistant (*cognitive remediation coach*). Participants assigned to the experimental software treatment program will be randomly assigned to receive performance feedback (version A.1 vs. A.2) in the first or the second half of training. Participants will then be asked to complete a mid-training assessment (V1.5) and will be administered a subset of assessments comprised of the secondary outcome: mindfulness. At the mid-training assessment, participants who were randomized to the experimental program will switch program versions (i.e., participants that trained on version A.1 will begin version A.2, and vice versa), such that participants train on both versions. To measure potential training-related improvements, participants will be assessed immediately after the completion of the total training (V2) by an assessor that is blind to group affiliation. To measure the persistence of potential training-related improvements, participants are also assessed after a three-month no-contact period (V3), again by an assessor blind to group affiliation. After this visit, participant activities are completed and trial participation ends.

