### Blinding

#### Un-blinded site roles

At each site, cognitive remediation coaches are un-blinded in order to provide support for participants using their assigned programs. They will be distinct from staff administering and scoring assessments. Additionally, site sub-investigators authorized to register participants within the ALERT system will remain un-blinded and may not participate in the assessment, evaluation, or follow-up of study participants.

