The current study is designed to the highest standard of RCT (e.g., blinded and deals with appropriate allocation concealment). Moreover, this protocol will measure immediate as well as lasting benefits of treatment. Lastly, many previous studies lacked statistical power due to a small sample size. ALERT is appropriately powered to detect improvements in targeted cognitive operations. We have statistically powered the study to detect a between groups Cohen’s d effect size of 0.50 on an outcome measure, calculated as the between group difference in the treatment effect means (post-assessment score minus pre-assessment score) divided by the pooled standard deviation of the observed test-retest reliability. This effect size translates, for example, in an improvement of 5.8 points (on an IQ-like index score) within the treatment group versus an improvement of 1.0 point within the active control group, with both groups showing a variance of 10 points (2/3 of a standard deviation, as observed in other composite cognitive performance data) from pre-assessment to post-assessment. Recently published studies that examined the efficacy of the core exercise (TAPAT) in participants with acquired brain injury (*n* = 40) documented effect sizes of 0.75 [32] and 0.69 [33] on the composite attention measure; we believe this is a reasonable estimate of the plausible effect size in this trial. Also, a recent meta-analysis of the effect size of cognitive rehabilitation documented an average between groups effect size of 0.31 [58] in the population of studies used to support the practice guidelines for cognitive rehabilitation [59, 60]. Based on this analysis, we will enroll 120 participants into the trial. We intend to enroll equally from each site (60 per site).

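### Randomisation is stratified by age but not by site, which allows avoidable chance imbalance of the arms within the two sites, and a random site factor does not remove a site difference in pre-to-post change

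*Protocol article*

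**What the plan says.** Under Randomization, the article specifies a "random permuted blocks within strata procedure [49, 50] with strata as age" (65–74, or 75 and over), and "allocation ratio is 1:1". The server is described as "implementing an automated centralized group assignment procedure with allocation concealment". No other stratification factor is named.

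Under Overall design and timeline there are two sites: "Assessments will be performed at University of Iowa (Iowa City, IA) and VA Boston Healthcare System (Boston, MA". The same section compares 60 participants per arm: "Sixty older adults completing TAPAT will be compared to sixty older adults completing the active control condition". The Strengths section gives the total, "Based on this analysis, we will enroll 120 participants into the trial", and the split by site: "We intend to enroll equally from each site (60 per site".

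Staff are organised by site. "At each site, cognitive remediation coaches are un-blinded in order to provide support for participants", and under Blinded site roles the tests are administered and scored by blinded staff of each site. Under Un-blinded site roles, the sub-investigators who register participants are unblinded.

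Under Data analysis, the linear mixed model has group and time as fixed factors and site as a random factor. The test is the group by time interaction.

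**The concern.** Blocks run within two age strata pooled over Iowa and Boston, so nothing holds the arms level within a site. The sites differ in coaches, examiners and recruitment sources. Coaching bears on adherence to home training, so sites could differ in how much participants change, and not only in their score level.

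If such a difference exists and one site happens to hold more TAPAT participants, part of it enters the treatment estimate in that realised randomisation, in either direction. A random site intercept shifts both visits of a participant alike and leaves a site difference in change untouched. A variance estimated from two sites is also poorly determined. Uneven arms within a site also make it harder to check whether the effect is consistent across sites.

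**Working it through.** The article states no figure for within-site balance, so there is none to reproduce.

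**Inputs from the article.** N = 120, 60 per arm, 60 per site, 1:1 allocation, age-only strata, planned d = 0.50 on pre-to-post change.

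**Assumptions.** Two-sided 5% test. Block sizes of 4, 6 or 8 and 40% of participants aged 75 or over (for the simulation only). Site difference in mean change of 0.1 to 0.5 SD. The article gives none of these.

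**1. Chance split within a site.** With 60 of 120 on TAPAT and 60 at a site, the number k on TAPAT at that site is hypergeometric with mean 30:

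- Variance = 60 × 0.5 × 0.5 × (120 − 60)/(120 − 1) = 7.56, so SD = 2.75
- P(33/27 or worse) = 36%
- P(34/26 or worse) = 20%
- P(35/25 or worse) = 10%
- P(36/24 or worse) = 4.4%

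Simulated age-stratified blocks of 4, 6 and 8 with randomly mixed site accrual give SDs of 2.73, 2.75 and 2.77. Blocking within age therefore does not help balance within site.

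**2. Effect on the estimate.** If k = 35 at one site, it is 25 at the other. The arms then differ in site mix by 35/60 − 25/60 = 10/60 = 0.167. The shift in a treatment difference not adjusted for site by time is 0.167 × the site difference in change. The standard error is √(2/60) = 0.183 SD.

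| Assumed site difference in change (SD) | Shift at 35/25 (SD) | Share of standard error | Share of d = 0.50 |
|---|---|---|---|
| 0.1 | 0.017 | 9% | 3% |
| 0.2 | 0.033 | 18% | 7% |
| 0.3 | 0.050 | 27% | 10% |
| 0.5 | 0.083 | 46% | 17% |

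**3. Average case.** The mean of |k − 30| is about 2.2, so the mean absolute difference in site mix is 2 × 2.2/60 = 0.073. The average absolute shift is 0.073 × 0.1 = 0.007 SD to 0.073 × 0.5 = 0.037 SD. The signed average is zero.

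**4. Site added as a stratum.** In the same simulation the SD of k falls to 0.63, 0.75 and 0.87 for blocks of 4, 6 and 8, with a 95% range of 30 ± 1 to 2. N stays at 120, in four strata averaging 30.

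**5. Cost of adjusting for site in the model.** At 35/25 the correlation of arm with site is 2 × 5/60 = 1/6, so the variance factor is 1/(1 − 1/36) = 1.029. Power at d = 0.50 (normal approximation) goes from 78.2% with 60 per arm to 77.0% with an effective 60 × 35/36 = 58.3 per arm. Averaged over randomisations the factor is about 1.008.

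**The case against.** A reader might infer that coach or examiner effects are confounded with treatment, or that the effect estimate is biased. The documents do not support that. No section ties coaches or assessors to one arm, assessors are blinded, and central 1:1 blocks within age strata are valid randomisation. The imbalance has expectation zero, and site variation left in the residual is already in the standard error, so the 5% error rate holds over repeated randomisation. Constant site differences in examiner severity or participant level cancel in each participant's change. All of this stands and limits the point to chance imbalance.

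The size also rests on a site difference in change for which the article gives no basis. The upper end, 0.5 SD, equals the whole planned effect. This stands too, which is why a range is shown.

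Site is already in the model, and the article does not spell out the random-effects structure; an analysis plan not shown here may do so. The article would also adjust for baseline factors that differ between arms at p < 0.1. A 35/25 against 25/35 split gives chi-square = 120 × (35² − 25²)²/60⁴ = 3.33, p = 0.068, so site could qualify if it counts as a characterisation variable. This stands only in part: a main effect of site, fixed or random, does not remove a site by time difference.

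Finally, site-specific blocks make the next assignment easier to guess for registering staff, who are unblinded and see earlier allocations at their own site. This is a genuine trade-off. Concealed, varying block sizes largely meet it.

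**Conclusion.** The point holds as a minor, avoidable design weakness. Age-only strata leave a 10% chance of a 35/25 split or worse within a site, and the stated site term, read as a random intercept, does not absorb a site difference in change. At that split the estimate moves by 0.017 to 0.083 SD if the sites differ in change by 0.1 to 0.5 SD, which is an assumption. The typical shift is less than half as large. The validity of the randomisation and the type I error rate are not in question. The change is worth making because it is cheap and needs no more participants.

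**What to change.** Set the server strata to age group (65–74; 75 and over) by site (Iowa; Boston). This gives four strata with 1:1 allocation and varying block sizes concealed from the sites, because the staff who register participants are unblinded. In the primary model, replace the random site factor with fixed terms for site and site by time.

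If enrolment is already advanced, the model change alone suffices; write it into the plan before allocation is revealed for analysis. The randomised order of the two TAPAT versions can stay as it is, since it does not bear on the comparison with the control.

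The cost is a server setting and short edits to Randomization and Data analysis, a few more incomplete blocks at the end of recruitment, and slightly greater predictability within a site. If the split reaches 35/25, the model adjustment costs the variance factor of about 1.03 shown above.

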### Blinding

#### Un-blinded site roles

At each site, cognitive remediation coaches are un-blinded in order to provide support for participants using their assigned programs. They will be distinct from staff administering and scoring assessments. Additionally, site sub-investigators authorized to register participants within the ALERT system will remain un-blinded and may not participate in the assessment, evaluation, or follow-up of study participants.

#### Blinded site roles

All site staff responsible for the administration and scoring of participant assessments will remain blinded to participant treatment. Site Principal Investigators will be required to complete a Delegation of Authority Form prior to the start of the study, indicating which activities individual site research team members will be authorized to complete. Site Principal Investigators will also remain blinded.

To prevent un-blinding, the following controls will occur at the site level:The treatment condition and the control condition will be identified as “Treatment A” and “Treatment B”;Participants will be reminded not to discuss details related to treatment with psychometricians and/or clinical evaluators during the informed consent process as well as prior to initiation, and at the conclusion of, each assessment visit;Site personnel will be instructed to not discuss details of either treatment arm during open participant groups or forums;Sites will be required execute the protocol in a manner that minimizes the possibility of accidental un-blinding of psychometricians or clinical evaluators (e.g. unintended viewing of treatment sessions);Sites will be asked to post signage in appropriate areas throughout the facility reminding staff and participants to not discuss treatment details in open locations.

At the half-way point of the trial, and at the end of the trial, psychometricians will be asked questions designed to evaluate the integrity of the blinding procedures employed throughout the study.

### Description of treatment program

*The Experimental Treatment Program* is a computerized cognitive remediation program consisting of a set of specific cognitive exercises. Participants perform tens to hundreds of trials over the course of a session, with auditory and visual feedback and rewards to indicate if the trial was performed correctly or incorrectly (version A.1). After each session, the difficulty of the next session is updated (e.g., less inter-stimulus-interval jitter) to ensure that each participant is appropriately challenged. Summary screens including game metrics (points, levels) and exercise metrics (usage, progress) are shown to the participant at the end of each session (version A.1).

There are two versions of the experimental software treatment program, TAPAT. One version provides participants with real-time feedback on their training performance (version A.1), while the other version does not provide participants with performance feedback (version A.2). A description of exercises in experimental treatment program is as follows:

The primary component of the experimental treatment program, *Tonic and Phasic Alertness Training (TAPAT),* is comprised of three variations designed to improve the individual’s intrinsic regulation of alertness and executive control. Specifically, the ability to sustain attention and respond to successively presented stimuli in a consistent manner (i.e., low reaction time variability), and ability to inhibit the proponent motor response when a target is presented. Exercise variants: 1) *Freeze Frame*, a visual category-nonspecific version; 2) a visual, within-category version; 3) a visually engaging, category-nonspecific version (Fig. 2).

**Fig. 2 Fig2:**
[figure not shown]
A visual, within-category version A.2 of TAPAT (without feedback)

In version A.1, real-time performance feedback is provided in each exercise at five distinct times, at 20% completion intervals for that exercise. Participants are instructed to be mindful of their performance and to make an effort to maintain a performance goal of 20/20 for each interval (Fig. 3).

**Fig. 3 Fig3:**
[figure not shown]
Version A.1 of TAPAT with performance feedback provide every ~ 2 min in the form of an accumulated score (max = 20 per two minutes; total score max = 100)

All training sessions will consist of the three variations of TAPAT to provide variety during each training session. A summary of the training schedule is provided in Table 1.

**Table 1 Tab1:** Training Schedule for a participant randomized to receive TAPAT with feedback in the first half of training

Sessions 1–18	TAPAT with Feedback (v.A.1)	(32 min/session)
	TAPAT (10 min) > 60 s break> TAPAT (10 min) > 60 s break > TAPAT (10 min)	
V1.5	Mid-training assessment (V1.5) Subset of assessments administered in-person.	
Sessions 19–36	TAPAT without Feedback (v.A.2)	(32 min/session)
	TAPAT (10 min) > 60 s break> TAPAT (10 min) > 60 s break > TAPAT (10 min)	

*Active Control Program (commercially-available computer games):* The active control program is composed of 6 commercially available computer games and is designed to: 1) be a face-valid approach to treating cognitive remediation age-related decline (analogous to crossword puzzles for age-related cognitive decline), ensure that participants remain blind to group affiliation, and match the experimental treatment program in halo or expectation-based influence on performance in neuropsychological outcome measures; 2) match the experimental treatment program in overall program use intensity, time-spent attending, delivered rewards, and overall engagement; and 3) provide a comparison group that matches the experimental treatment group on the aforementioned attributes, but without the known therapeutic elements.

### Foreseeable risks, Risk Management & Emergency Response

Participation in the study presents minimal risk. The probability and magnitude of harm or discomfort anticipated in this research study are not greater than those ordinarily encountered in daily life or during the performance of routine physical or psychological examinations or tests. Study participation may be discontinued when a participant voluntarily withdraws from the study (e.g. due to scheduling issues or changing residence) or when they express discomfort with any of the study procedures (e.g. excessive frustration, boredom, or eye strain). To improve adherence to the interventions, weekly check-ins were performed to monitor participants’ progress, motivate and provide feedback, and allow participants to voice any adverse effects.

Serious adverse effects from prior studies of the treatments under study have not been reported. The protocol details potential risks related to study participation and includes assessments of depression and suicidality at baseline, week 13, and week 26 (end-of-study). Participants will be encouraged to report any adverse effects occurring during the duration of the study to the point of contact within research staff. PSC does not provide compensation for research-related injuries and will not reimburse or pay medical expenses for the treatment of research-related injuries.

We will conservatively follow guidelines for medical devices in the reporting of adverse events in this trial, which defines unanticipated adverse device effects (UADEs) in The Code of Federal Regulations in 21 CFR 812.3(s) as any serious adverse effect on health or safety of any life-threatening problem or death caused by, or associated with, a device, if that effect, problem, or death, was not previously defined in nature, severity or degree of incidence in the investigational plan or application (or supplementary plan or application). Furthermore, an effect is classified as an UADE if it is judged by the Site PI to be a serious problem associated with a device that related to the rights, safety, or welfare of participants. We will operationalize this definition of a serious problem as one that results in any of the following outcomes: death, life-threatening situation, inpatient hospitalization atypical of the participant’s diseases condition, persistent or significant disability/incapacity; or any other adverse event that, based upon appropriate medical judgment, may jeopardize the participant’s health or the health and well-being of all participants enrolled in the study.

Site Study Coordinators, Psychometricians, and Cognitive Remediation Coaches will ask about any UADEs during each contact with participants and will be alert to any volunteered UADEs. All UADEs will be documented on a standardized eCRF and will be classified by the blinded Site PI to their degree of seriousness and their relationship to the study software.

All UADEs, whether or not we believe them to be related to the protocol, will be reported to the Site IRB according to the investigational site’s IRB procedures and to Study PI ([name]) as soon as possible, but in all cases within 10 working days of the event. PSC will circulate UADE reports to the Research Monitor and all trial sites within 10 working days of receipt. Each study site will report immediately to: 1) University of Iowa IRB, 2) PSC IRB, or 3) At the Boston VA, UADEs will be reported to the VA Central IRB electronically through a secure SharePoint system and confirmed by phone to [name].

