**Methods/design:**

We will employ a multi-site, longitudinal, blinded randomized controlled trial (RCT) design with a target sample of 120 patients with age-related cognitive decline. Patients will be asked to complete 36 training sessions remotely (30 min/day, 5 days a week, over 3 months) of either the experimental TAPAT training program or an active control computer games condition. Patients will be assessed on a battery of cognitive and functional outcomes at four time points, including: a) immediately before training, b) halfway through training, c) within forty-eight hours post completion of total training, and d) after a three-month no-contact period post completion of total training, to assess the longevity of potential training effects.

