#### Exclusion criteria

Diagnosis of PTSD, depression or other psychologically diagnosable emotional disorder as verified via participant self-report, and performance on the Geriatric Depression Scale (GDS ≥ 20). If the participant has previously had a psychologically diagnosable Axis I emotional disorder and they have not experienced an episode for more than 2 years, they may be included.Diagnosis of an illness or condition with known cognitive consequences (e.g., schizophrenia, bipolar disorder, cancer, multiple sclerosis) will be excluded due to the confound with cognitive impairment from those conditions. If the participant has received 5 or less doses of chemotherapy in the two years preceding potential enrollment, they may be included. These exceptions are up to the discretion of the Study Principal Investigator and Site Principal Investigators.Participants who have answered ‘yes’ to:
Question 5 (Active Suicidal Ideation with Specific Plan and Intent) on the Columbia-Suicide Severity Rating Scale (C-SSRS) or,‘Yes’ to any of the suicide-related behaviors (actual attempt, interrupted attempt, aborted attempt, preparatory act or behavior) on the “Suicidal Behavior” portion will be excluded from the study *if the ideation or behavior occurred within two months from Participant’s date of consent* (as recommended by the FDA for treatment trials.) Participants excluded for this reason will be referred for appropriate treatment. Further, participants meeting this criteria at any time throughout the study will be asked to complete a final assessment, if appropriate, then withdrawn from the study and referred for appropriate treatment.
4)Current or significant past history of substance abuse in the judgment of the Site PI.5)Difficulty completing assessments and/or comprehending requirements of the trial (e.g., following verbal instructions).6)Enrollment in a concurrent clinical trial involving an investigational pharmaceutical, nutraceutical, medical device or behavioral treatment that could affect the outcome of this study will be excluded. Participants will not be excluded for participation in conventional treatments (e.g., physical or occupational therapy) or use of prescribed medications.

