### Repeated assessment battery

Once a participant is deemed eligible for participation based on their V0 results, they are next scheduled for their baseline session on the repeated assessment battery (V1), which takes approximately two hours. After completing this baseline assessment, participants are randomly assigned to either experimental or control training conditions (see below). Then, following the program set-up visit and after completing the first half of the training sessions, they will be administered an abbreviated mid-training assessment (V1.5) comprised of mindfulness-related measures. Immediately after total training is completed, participants are re-administered the baseline assessment battery (V2) and again after a three-month no contact period (V3).

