### Data analysis

The data analysis plan a priori defines a primary intent-to-treat (ITT) population, a set of secondary evaluation populations, a primary outcome measure, a set of secondary outcome measures, a single primary evaluation time point, a secondary evaluation time point, a primary statistical analysis methodology, a criterion for statistical significance, and guidance for interpretation of results. There will be no interim analyses.

The primary ITT population is defined as all participants who complete a set-up (V1) visit. Note that this includes all randomized participants except those who drop/withdraw post-randomization and pre-setup visit. In total, there are three a priori defined analysis populations, including a primary analysis population (i), a secondary analysis populations designed to compare effect sizes in populations with no missing data (ii) and a tertiary analysis population who completed all training visits (iii)i.*Intent to Treat (ITT) population:* This is the a priori primary analysis population, defined as including all randomized participants who completed a V1.ii.*Intent to Treat (ITT) Fully-Evaluable (FE) population:* This is a secondary analysis population, defined as including all members of the ITT population that complete a V2 visit (the ITT-FEV2 population), or all members of the ITT population that completed a V3 visit (the ITT-FEV3 population). Note that a participant may complete a specific visit but have missing data for a test in which case the participants is in the overall FE population but does not contribute data to the FE population for that visit, e.g., the number of evaluable cases for a specific test on a specific visit may be smaller than the FE population for that visit because of missing data.iii.*Intent to Treat (ITT) Fully-Trained (FT) population:* This is a secondary analysis population, defined as including all members of the ITT-FE population who complete a target number of training visits (65 visits). Note that the FT populations are strict subsets of the FE populations; a person who completes the target number of training visits but does not complete the evaluation visit is not a member of the FT population.

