#### Weaknesses

There are also potential limitations. Due to the long duration and multiple components of our study, attrition rates may pose a potential limitation. Furthermore, lack of motivation could prevent timely completions of the self-initiated training program. With a standardized protocol, frequent check-ins, and regular feedback from our research assistants, we aim to limit dropout rate.

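### V2 is timed only from completing training, and expressed discomfort may end study participation, so early stoppers may have no primary outcome and maximum likelihood cannot correct a loss related to gain

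*Protocol article*

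**What the plan says.** Timing of V2. The Abstract (Methods/design) places it "within forty-eight hours post completion of total training". Overall design and timeline says "participants will be assessed immediately after the completion of the total training (V2) by an assessor that is blind to group affiliation". Repeated assessment battery says "Immediately after total training is completed, participants are re-administered the baseline assessment battery (V2". None of the three gives a time from randomisation. V3 follows three months later and so takes its timing from the same event.

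Leaving the study. Foreseeable risks, Risk Management & Emergency Response says that study participation may be discontinued on voluntary withdrawal, "or when they express discomfort with any of the study procedures (e.g. excessive frustration, boredom, or eye strain". The subject of that sentence is participation in the study, not use of the training program. Exclusion criteria provides an exit assessment for one group only: those who meet the suicidality criterion during the study "will be asked to complete a final assessment, if appropriate, then withdrawn from the study and referred for appropriate treatment".

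Analysis. Data analysis says of the ITT set: "This is the a priori primary analysis population, defined as including all randomized participants who completed a V1". The Fully-Evaluable set adds completion of V2 (or V3), and the Fully-Trained set is a strict subset of it. Missing data are handled by maximum likelihood in a linear mixed model, and the primary test uses baseline and post-training data. The mid-training visit cannot help, because "they will be administered an abbreviated mid-training assessment (V1.5) comprised of mindfulness-related measures". Weaknesses concedes that "attrition rates may pose a potential limitation" but gives no rate.

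**The concern.** The visit rules and the analysis sets do not fit together. The ITT set promises a comparison of everyone randomised with a V1, and the Fully-Evaluable set presupposes that some people attend V2 without full training. Yet V2 is timed only from an event that a person who stops never reaches, and expressing frustration or boredom may end that person's participation altogether.

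If early stoppers have no V2, the model predicts their outcome from completers in the same arm with the same baseline. That is sound only if, given baseline, arm and any model covariates, stopping is unrelated to the gain they would have shown. Stopping out of frustration with an attention-training task could break that condition. The two programs also differ in kind, a continuous performance task against commercial games, so loss need not be equal. The ITT estimate could then drift towards a comparison of completers. A visit that was never held cannot be recovered by a later analysis plan.

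**Working it through.** **1. The plan's own figure.** Discussion (Strengths) gives d = 0.50 and 120 participants, 60 per arm, but states no power, sidedness or dropout allowance. At two-sided 0.05, 60 per arm gives 78.2% power (normal approximation; 77.5% by noncentral t), and 80% would need 63 per arm. With power unstated, 120 can be neither reproduced nor refuted, and the point does not depend on it. It matters here only because 0.50 is the yardstick for bias. Any 15% loss, informative or not, lowers power to 71.4% (51 per arm, normal approximation).

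**2. What an early stopper contributes.** Baseline: yes. V1.5: no component of the primary composite. V2: none, unless a visit is arranged that the stated timing does not cover. The likelihood therefore has one observation for that person and no intermediate value of the outcome.

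**3. Bias formula.** Let q be the share of an arm without V2 and g the amount, in SD of change, by which their unobserved change falls short of completers' with the same baseline. If completers change by m, the arm's true mean is (1 − q)m + q(m − g) = m − qg. Using m overstates it by qg, so

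bias = q_T·g_T − q_C·g_C (T = TAPAT, C = control).

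All values of q and g below are assumptions. A positive sign favours TAPAT.

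| Dropout T / C | Gap, same in both arms | Bias (SD) | Two-sided type I error |
|---|---|---|---|
| 10% / 10% | any of 0.25, 0.5, 1.0 | 0 | 5% |
| 20% / 10% | 0.25 | 0.10 × 0.25 = +0.025 | 5.2% |
| 20% / 10% | 0.5 | 0.10 × 0.5 = +0.05 | 5.7% |
| 20% / 10% | 1.0 | 0.10 × 1.0 = +0.10 | 8.0% |
| 10% / 20% | 0.25 to 1.0 | −0.025 to −0.10 | as above, by symmetry |

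The standard error for 20% / 10% is √(1/48 + 1/54) = 0.198. Equal dropout alone does not guarantee zero, since the gaps must match too. With 20% lost in each arm, g_T = 0.5 and g_C = 0, the bias is 0.20 × 0.5 = +0.10.

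**4. Loss in one arm only.** If the tendency to leave has correlation r with poorer change, completers' mean change is too high by r·φ(z_q)/(1 − q). For q = 0.20, φ(−0.842)/0.80 = 0.280/0.80 = 0.35. So r = 0.2, 0.3, 0.5 gives 0.07, 0.105, 0.175 SD, in favour of whichever arm suffers the loss.

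**5. Check with the maximum likelihood estimator itself.** A simulation of the two-time-point model used 60 per arm, no true effect, an assumed baseline–V2 correlation of 0.7 and 4,000 runs. Results for 20% / 10% dropout:

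- Dropout by baseline only: bias 0.004, type I error 5.1%. Maximum likelihood does its job.
- Dropout correlated 0.3 with poorer change in both arms: bias +0.042, type I error 5.7%.
- Exactly the worst changers lost: bias +0.139, type I error 18.1%. Part of that excess is a standard error that is too small, because even 10% / 10% under this mechanism gives 9.0% with no bias.

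**The case against.** The strongest reply is that the three timing statements describe the ordinary participant and bar nobody from V2. A Fully-Trained set nested strictly within a Fully-Evaluable set makes sense only if some people attend V2 without full training. There is also some calendar frame: depression and suicidality are assessed at weeks 13 and 26, and training is expected to take about 12 to 16 weeks. Those who stop stay in the ITT set. The discomfort rule is permissive and sits in a section on participant risk. The control program is designed to match TAPAT on intensity of use, rewards and engagement, and weekly check-ins support adherence. Finally, an article condenses a fuller protocol, where an early-termination visit may be specified.

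Most of this stands, and it rules out three stronger readings that a reader might infer:

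- That the ITT analysis drops these participants. It does not. What may be lost is their V2 value.
- That those lost are exactly the ones who fare poorly. Nothing in the article links boredom or eye strain to poor change in executive function.
- That loss will be heavier under TAPAT. That is possible, but the article neither shows nor implies it.

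What the reply does not remove is the mismatch between stated rules. The nested sets need V2 visits that none of the three timing statements places in time. Weeks 13 and 26 are given for safety scales and are not tied to V2. The article does describe an exit assessment, but only for the suicidality withdrawal.

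**Conclusion.** The point holds as a defect in the stated visit rules with a possible, unproven bias. V2 is anchored to completion of training, discomfort may end study participation, and the analysis sets assume that non-completers can be observed. Following the visit rules as written may leave early stoppers with baseline data only, and maximum likelihood cannot repair a loss that depends on the unseen gain.

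The likely size is modest. In the 20% versus 10% scenarios it is 5% to 20% of the planned 0.50 (0.025/0.50 to 0.10/0.50). If 20% of one arm only is lost, with an exit–change correlation of 0.2 to 0.5, it is 14% to 35% (0.07/0.50 to 0.175/0.50). It is about zero under equal dropout and equal gaps or under baseline-only dropout, and it works against TAPAT if the control arm loses more. The simulated +0.14 SD belongs to a limiting case and should not be taken as an expectation. Dropout rates, gaps and correlations are all assumptions, because the article supplies none.

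**What to change.** First check whether the full protocol already provides for this. If not, reconcile the V2 timing in the Abstract, Overall design and timeline, and Repeated assessment battery, together with the discontinuation sentence under Foreseeable risks, with the populations in Data analysis:

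- Distinguish stopping training from leaving outcome follow-up.
- For participants who do not finish training, give V2 and V3 a window counted from randomisation, and invite them to these visits where they remain willing and it is appropriate.
- Record the reason for stopping, by arm.
- State what counts as completed training. The schedule has 36 sessions, while the Fully-Trained set requires 65 training visits; the two must be reconciled.

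The withdrawal on the suicidality criterion and any clinical stopping rule are outside this change and stay as written. A missing-data sensitivity analysis belongs in the analysis plan and cannot stand in for visits that were not held.

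The cost is a few sentences and a few visits of a kind already planned for every participant. The estimate may come out slightly smaller because it includes people who did not finish, but it is then closer to the comparison that the ITT definition promises.
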